
#### Dietary intake

Daily dietary intake will be assessed for the following food groups: wholegrain and white bread (slices), dinner portions (spoons), regular soft drinks and alcohol (glasses), *light *soft drinks (glasses), sweet and salty snacks (pieces), vegetables and fruits (pieces or portions), fish and crustaceans (portions). Of these food groups, average intake on days per week and slices/spoons/glasses/pieces/portions per day during a usual week in the past month will be indicated. High intake of regular soft drinks, alcohol and snacks is considered as unhealthy dietary behaviour, whereas high intake of light soft drinks, vegetables, fruits and fish is considered as healthy dietary behaviour. The questions about fruits and vegetables were derived from the short questionnaire for measuring fruit and vegetable intake, developed by Maastricht University [46]. This questionnaire was shown to be sufficiently reproducible (*r*_*Spearman *_0.79 after 1 year) and appeared to be suitable for ranking individuals according to their consumption of fruits and vegetables and according to changes in their consumption, at least in females. As we learned from the interviews, total daily food intake in this population is relatively high. Therefore, the items 'bread' and self-rated 'portions for dinner' were added to assess the daily 'amount' of food intake. All of these food groups may be targeted in the energy balance intervention, depending on the participants' actual diet.

#### Smoking

Current smoking status (smoker or non-smoker) will be assessed by a single item.

#### Biomedical variables

BMI (kg/m^2^), systolic and diastolic blood pressure (mmHg), HDL-cholesterol, total cholesterol (mmol/l) and HbA1c (%) will be assessed by an occupational nurse at the PHS. First, weight will be measured on a digital balance, without shoes and jacket. After that, blood pressure will be measured once, by manual inflation, while the worker is seated. In most OHSs, a Maxi Stabil 3 measuring instrument (Speidel & Keller) will be used for this purpose. Finally, for the determination of HDL-cholesterol, total cholesterol and HbA1c levels venous blood will be drawn from the lower arm and transported to the laboratory for analysis. For each of these 3 measures 1.6 ml blood will be used. As described in the introduction, elevated BMI, blood pressure and cholesterol are indicators of CVD risk. HbA1c, a measure of haemoglobin glycosylation, is an indicator of the mean blood glucose level of the past 6–8 weeks [47]. Elevated HbA1c was shown to be an independent risk factor for coronary heart disease in persons with and without diabetes [48].

### Secondary outcome measures

#### Cardio respiratory fitness

CRF will be measured in an indirect way, by means of a predictor rule that was developed by an international group of experts in the fields of epidemiology, fitness assessment and preventive medicine, and has been shown to be a reasonably accurate measure of VO_2_max [49]. Using this prediction rule, VO_2_max is estimated from BMI, age, gender, resting heart rate (HR) and self reported data on habitual PA levels. The outcome of this prediction rule is indicative of a person's maximal workload expressed as METs; a measure for CRF. Resting HR is not assessed in the PHS and can neither be added for practical means. Therefore, it will be measured by the counsellor at the first face-to-face encounter. At the follow-up health check-ups after 6 and 12 months HR will be measured again, only in the intervention group. For measuring resting HR a heart rate instrument (Polar S610, Polar Electro Oy, Finland) will be used. The participant will take off his shirt and lie down on examination bench. The Polar belt will be tied around his breast. The counsellor will read the HR from the Polar watch, 10 seconds after it has reached the lowest frequency, and record this figure on the registration form.

#### Sedentary activities

In leisure time, the study population is relatively sedentary. Sedentary behaviour is characterised by pursuits that require minimal amounts of energy, e.g. television watching and computer use. Several studies have shown that sedentary behaviour is, independently from the PA level, a risk factor for CVD [50,51]. Using the AQUA questionnaire, previously used by Slootmaker *et al.*[52], we will assess the days per week and minutes per day spent on television watching, computer use, sitting in a car or other sedentary activities in a usual week during the past month.

#### Stage of change

The 'stage of change' items in the questionnaire are based on the stages as defined in the PAPM. The stage of change for *eating less or healthier *as well as the stage of change for *becoming more physically active *will be measured using a single question with 5 outcome categories, of which the participant needs to choose the most appropriate. For PA, these categories are: "I have never thought about becoming more physically active"; "I have thought about becoming more physically active, but I do not know (yet) whether I will do so"; "I have decided not to become more physically active"; "I have decided to become more physically active but I am not currently doing so (yet)"; "I think I am already physically active enough". The questions were derived from Wammes *et al.*[53], who applied the PAPM to a non-obese population in a study aimed at weight gain prevention, following Weinstein's staging algorithm. The validity and reliability of this questionnaire have not yet been tested.

#### Behavioural determinants

As described before, attitude, social influence and self-efficacy are important determinants of behaviour (change) and will be addressed in the intervention. Therefore, attitude (on a 5-point Likert scale ranging from *very bad *to *very good*), self-efficacy (on a 5-point Likert scale ranging from *very difficult *to *very easy*) and social influence of partner, relatives, colleagues or friends (on a 5-point Likert scale ranging from *not at all *to *very much*) will be measured. The same determinants will be measured for *becoming more physically active*. The items about attitude and self-efficacy were derived from Oenema *et al.*[54].

#### Sickness absenteeism

Each participant will be asked to fill in 'total days absent from work' in the past 2 months. Since the difference between registered and reported sick leave was shown to increase with an increasing recall period, Severens et al. (2000) suggested a recall period of no more than 2 months [55]. Therefore, besides the questionnaires at baseline, 6 and 12 months, an additional short questionnaire measuring sickness absenteeism only will be sent to all participants after 2, 4, 8 and 10 months. Participants will not only be asked to report their sickness absenteeism in general, but also their sickness absenteeism due to sports injury, as sports injuries may result form the intervention.

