#### Step 2: Choosing type of intervention

Two types of intervention will be offered: 1) an energy balance intervention and 2) a smoking cessation intervention. Together with the counsellor, the smoker will choose one of the two intervention types, based on his personal risk profile and his own preferences. He will be encouraged to make his choice during the first meeting, and to stick to his first choice. However, if later on during the intervention, the participant desires to switch intervention types or if he prefers to address both smoking and energy balance, this will be possible. In case a participant is not ready make his choice in the first meeting yet, e.g. because he is confused by his risk profile, he will be allowed to make his choice during the 2^nd ^contact. In the energy balance intervention, both diet and PA will be addressed. Depending on the current PA and dietary behaviour of the participant, the focus will be on diet or daily PA. In improving dietary and PA behaviour, sub-behaviours will be chosen to address, which will be relevant to the participant and feasible, e.g. reducing fat intake or cycling in leisure time.

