### Primary outcome measures

#### Physical activity

The main outcome measure for PA is whether the participant has started to fulfil one or both of the Public Health recommendations for PA. If so, he is considered to have changed from physically inactive to physically active.

On the PHS questionnaire, he will fill in how many days per week he usually is moderately physically active for more than 30 minutes. From this item, fulfilling the Public Health recommendation for moderate PA can be determined. Furthermore, he will be asked how many days during the last month he has performed vigorous physical activities that lasted long enough to make him sweat. By this item, fulfilling the Public Health recommendation for vigorous PA can be computed. Another outcome measure for PA is the frequency, duration and intensity of PA in leisure time. This will be assessed using the Short QUestionnaire to ASsess Health enhancing physical activity (SQUASH), which was shown to be a fairly reliable and valid questionnaire (*r*_*Spearman *_0.58 and *r*_*Spearman *_0.45 respectively) [44]. The SQUASH was designed to measure four clusters of PA, i.e. commuting activities, household activities, activities at work and school, and leisure time activities. For the purpose of this study, only commuting activities and leisure time activities, i.e. walking, cycling, gardening, odd jobs and sports will be measured, as these activities are considered relevant for the target group. The participant will be asked to fill in how many days per week and how many minutes per day he usually spends on these physical activities, during a usual week within the past month. The level of exertion for each type of activity will have to be indicated as well. The level of exertion for sports, gardening and odd jobs is classified as light, intermediate, and vigorous. The level of exertion for walking and cycling is classified as slow, intermediate, and fast. From the SQUASH, metabolic equivalents (METs) can be estimated. Light activities are rated as 2.0 to < 4.0 METs, moderate activities are rated as ≥ 4.0 to <6.5 METs, vigorous activities are rated as ≥ 6.5 METs [44]. The cluster items about household activities will be left out of the SQUASH questionnaire, as we expect these activities not to be major contributors to daily PA in this population of male construction workers. In addition, the SQUASH items about activities at work and school were not considered suitable for our population. The level of exertion, i.e. light, intermediate, or vigorous, of the daily activities at work will be assessed using a single question derived from the TNO questionnaire PA at work [45], which has not been tested for validity and reliability yet.

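### Injury from the intervention is foreseen but measured only as work absence due to an undefined sports injury, so unchanged sports-injury absence could not be read as no increase in injury

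*Protocol article*

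**What the plan says.** The harm and its measure appear together in the protocol article, under Secondary outcome measures, Sickness absenteeism. The unit is self-reported days off work with a two-month recall: "Each participant will be asked to fill in 'total days absent from work' in the past 2 months". The same section adds a split by cause: "but also their sickness absenteeism due to sports injury, as sports injuries may result form the intervention". The main questionnaires come at the start and at the two follow-up measurements; to fill the intervals between them, "an additional short questionnaire measuring sickness absenteeism only will be sent to all participants after 2, 4, 8 and 10 months".

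Activity is defined more widely. Under Primary outcome measures, Physical activity, the activity questionnaire is cut down so that "only commuting activities and leisure time activities, i.e. walking, cycling, gardening, odd jobs and sports will be measured". Sports is one type in that list and is rated alongside others: "The level of exertion for sports, gardening and odd jobs is classified as light, intermediate, and vigorous". In the counselling protocol, Step 2, sub-behaviours are chosen "which will be relevant to the participant and feasible, e.g. reducing fat intake or cycling in leisure time".

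The article does not define a sports injury and does not show the wording of the item.

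**The concern.** The authors give possible injury as their reason for asking, but the item records something narrower, in two respects.

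- **Absence.** An injury counts only if it leads to sick leave. A man who is hurt and keeps working contributes zero days.
- **Sports.** The intervention may steer a man towards cycling, and the activity questionnaire counts his walking, cycling, gardening and odd jobs. If he is hurt doing one of these and stays home, his days enter total absence. Whether they also enter the sports-injury split depends on how he reads the term.

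Activity is therefore measured over a wide range, and injury over a narrower and less certain one. What is at stake is interpretation. A report of no increase in sports-injury absence would invite the reading that counselling did not raise injuries, and the item cannot support that reading.

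**Working it through.** **Background check of the plan's own figure.** The sample size section gives 38% v 28% inactive, 80% power and alpha 0.05. The two-proportion formula (two-sided, pooled variance, no continuity correction) gives 346 per group, 692 in total, with power 0.800. The plan's figure reproduces. The point does not depend on it, but 346 per arm is used below as the evaluable number.

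**Timing.** A two-month recall at months 2, 4, 6, 8, 10 and 12 covers 0–2, 2–4, 4–6, 6–8, 8–10 and 10–12 months. The year is covered in both arms without a gap. The weakness lies in what is counted, not when.

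**What the described sources would capture.**

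| Event | Total absence | Sports-injury absence |
|---|---|---|
| Sports injury, days off | yes | yes |
| Sports injury, no days off | no | no |
| Walking, cycling, gardening or odd-job injury, days off | yes | depends on the man's reading of the term |
| Same, no days off | no | no |

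No other source described in the article covers both arms for injury. The co-intervention items concern other risk-related care and lifestyle change. The counsellor forms record contact details, topics and goals, and the process questions ask for opinions. These last two exist only in the intervention group.

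**Size, for illustration.** The article gives no injury rates, so all rates here are assumptions. Let p1 and p2 be the 12-month risks of an activity injury in the control and intervention arms, f the fraction of injuries that cause absence (the same in both arms), and n = 346 per arm. The item then sees risks f·p1 and f·p2. With q1 = f·p1, q2 = f·p2 and q̄ their mean,

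power = Φ{ [ (q2 − q1)√n − 1.96·√(2q̄(1 − q̄)) ] / √(q1(1 − q1) + q2(1 − q2)) }.

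- p1 = 10%, p2 = 16%, f = 1: (0.06 × 18.60 − 1.96 × 0.4756)/0.4737 = 0.388, power 0.65.
- f = 0.3, so 3.0% v 4.8%: (0.018 × 18.60 − 1.96 × 0.2738)/0.2735 = −0.738, power 0.23.

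The next table uses the same formula over a range, holding the risk ratio at 1.6. Each cell shows expected men with an event (control v intervention), then power.

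| Assumed injury risk | f = 1 | f = 0.5 | f = 0.3 | f = 0.1 |
|---|---|---|---|---|
| 5% v 8% | 17.3 v 27.7; 0.36 | 8.7 v 13.8; 0.20 | 5.2 v 8.3; 0.13 | 1.7 v 2.8; 0.07 |
| 10% v 16% | 34.6 v 55.4; 0.65 | 17.3 v 27.7; 0.36 | 10.4 v 16.6; 0.23 | 3.5 v 5.5; 0.10 |
| 20% v 32% | 69.2 v 110.7; 0.95 | 34.6 v 55.4; 0.65 | 20.8 v 33.2; 0.42 | 6.9 v 11.1; 0.17 |

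In every row the ratio stays at 1.6, because f cancels. What falls is the number of events and with it the precision. The f = 1 column is what a count of all injuries would see. In the middle row even that reaches only 65%.

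**The case against.** The strongest reply is that the item sits under sickness absenteeism and does what an absence outcome should: it separates absence that the intervention may itself cause. The article never calls it an injury endpoint. That stands, and it is why the absence figure should be kept. It does not remove the point, because the stated reason for the split is that the intervention may injure people, and no other described item addresses this.

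A reader might infer more than the article supports:

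- **That the trial has no harm recording.** A condensed article commonly leaves general adverse-event recording to the full protocol, which is not shown. The point rests on how the described item is defined, not on a missing system.
- **That cycling, walking and gardening injuries are simply missed.** The term is undefined and some men may include a cycling fall. If there is absence, the days are still in the total. Only their attribution is unreliable.
- **That the measure is biased by job type.** The same injury may plausibly cost a blue-collar worker more days than a white-collar worker, but randomisation is individual and stratified by that factor, so the mix is balanced between arms.
- **That the comparison is biased towards zero.** With a common absence fraction the risk ratio is unchanged. The absolute difference is smaller because it describes a rarer event.
- **That roll-out would rest on this measure.** The abstract and the closing paragraph tie wider use to effectiveness and cost-effectiveness, not to a harm measure.

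A last objection has force against the remedy. Participants are not blinded, and men counselled on activity may report minor injuries more readily. Work absence, though also self-reported, is a more concrete threshold.

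**Conclusion.** The point holds as a limit on what the item can show. It is firm that an injury without absence is not recorded by the described measure. It is also firm that absence after an injury from a non-sport activity is not reliably identified as activity-related. The consequence is fewer events, less precision, and a null result that cannot be read as no increase in injury. The article contains no contradiction here, and the primary outcomes are untouched.

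The size is uncertain. The direction (fewer events at the same ratio, so less power) needs only a common absence fraction below one. The power figures, such as 65% falling to 23% or 10%, rest on assumed injury risks and absence fractions and are illustrative. This is a cheap improvement, not a defect that threatens the trial's main conclusions.

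**What to change.** In the questionnaires that both arms already receive at 2, 4, 6, 8, 10 and 12 months, put one question before the sports-injury absence item: any injury in the past two months during sports, walking, cycling (including commuting), gardening or odd jobs, and during which activity. Follow it with the days absent because of that injury. Report the number of men injured by arm alongside injury-related absence days. Keep the absence figure, since it is less sensitive to reporting, and interpret the two together.

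The cost is a slightly longer short form, which is currently limited to absence, and one more table. Two downsides should be stated in the report: some trivial injuries will be counted, and self-report may differ between arms because participants know their allocation. The change would not guarantee adequate power, but it would count the event that the authors say may occur.

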#### Cost-effectiveness

Next to investigating the effects of the intervention, the costs of the intervention will be compared to the effects. All costs for the development of the intervention, i.e. training and printing of brochures, as well as for the implementation of the intervention, i.e. (previously defined) reimbursements for participant's travelling expenses, counsellor's face-to-face and telephone contacts and occupational nurses' health checkups, will be recorded by the principal investigator. Incremental costs of the intervention group compared to the control group will be divided by incremental effects for each of the biomedical effect measures, e.g. BMI, total cholesterol and systolic blood pressure, separately.

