### Data analysis

On all outcome measures, intention-to-treat analyses will be performed. Both crude and adjusted linear and logistic regression analyses will be performed. In doing so, analysis for covariance will be conducted adjusting for the outcome variable measured at baseline. In the adjusted model, other potential confounders will be included as covariate, such as age and work activities. Furthermore, effect modification, e.g. by family history, will be checked. First of all, data will be analysed for the whole intervention group, that is, irrespective of the intervention received. Secondly, subgroup analysis will be done among those having received the smoking or the energy balance intervention. As all participants will have to indicate at baseline which lifestyle behaviour they prefer to change, the participants in each intervention subgroup will be compared to those in the control group having indicated the same type of intervention preference. Cost-effectiveness ratios will be calculated by dividing the difference between the mean total costs between the two study groups by the difference in the mean effects. For each outcome measure used in this evaluation, cost-effectiveness ratios will be presented graphically on a cost-effectiveness plane. To calculate the confidence intervals for the ratios, bootstrapping will be done. For all analyses, a significance of 0.05 will be applied. On the process evaluation, qualitative analyses will be performed.

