Studying the effects of this intervention is important, as it aims at a serious and increasing health problem. This type of intervention has not been evaluated in this specific setting and in this target group yet. If proven effective, the employee will benefit from an improved lifestyle and a reduced CVD risk, and the employer may benefit from healthier workers and lower absenteeism. If proven cost-effective, in the future the OHSs in construction industry may implement this intervention on a larger scale.

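### The cost list covers the intervention only while the analysis divides undefined total costs, and the planned bootstrap intervals for the ratios cannot be read when the effect difference may be zero

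*Protocol article*

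**What the plan says.** The Protocol article's Cost-effectiveness section sets the costs of the intervention against its effects. It lists what is recorded: "All costs for the development of the intervention, i.e. training and printing of brochures, as well as for the implementation of the intervention". The implementation items are "reimbursements for participant's travelling expenses, counsellor's face-to-face and telephone contacts and occupational nurses' health checkups, will be recorded by the principal investigator". Incremental costs are then "divided by incremental effects for each of the biomedical effect measures, e.g. BMI, total cholesterol and systolic blood pressure, separately".

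The Data analysis section forms the ratio by "dividing the difference between the mean total costs between the two study groups by the difference in the mean effects". It does not define total costs. It adds that, for each outcome used, "cost-effectiveness ratios will be presented graphically on a cost-effectiveness plane", and on precision: "To calculate the confidence intervals for the ratios, bootstrapping will be done". The type of bootstrap interval is not given.

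Two other sections describe data that could enter a cost total. Under Sickness absenteeism, days absent are asked for in the questionnaires at baseline, 6 and 12 months, and "an additional short questionnaire measuring sickness absenteeism only will be sent to all participants after 2, 4, 8 and 10 months". Absence from sports injury is asked for separately, because the intervention might cause it. Under Co-interventions, other care is recorded at baseline and follow-up, and care that follows from the counselling is foreseen (physiotherapy, dietician advice, nicotine replacement). No section says that either will be given a money value.

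The Discussion states that, if the intervention proves effective, "the employer may benefit from healthier workers and lower absenteeism". A separate sentence links wider use by the occupational health services to proof of cost-effectiveness.

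**The concern.** There are two linked problems.

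**Which costs enter the numerator.** One section lists intervention costs and the other speaks of total costs. If total means the list, the numerator ignores two consequences that the trial measures. Absence may fall through better health or rise through sports injury, and use of other care may rise because of counselling. The omission could push the ratio either way.

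**How uncertainty is expressed.** A ratio has no continuous ordering once its denominator can be zero. As the effect difference falls through zero, the ratio goes to plus infinity and returns from minus infinity. With a positive cost difference, a negative ratio means costlier and worse, yet it sorts below every favourable ratio. If absence were valued and the cost difference could also be negative, a negative ratio could equally mean cheaper and better. Limits read off such a list do not bound anything useful.

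At stake is whether the cost-effectiveness result, which the Discussion ties to wider implementation, can be interpreted.

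**Working it through.** **Sample size, for reference.** The economic evaluation has no stated figure of its own. The plan's 346 per group reproduces for 38% versus 28%, two-sided alpha 0.05, 80% power and no continuity correction. Inflating for 20% loss gives 346/0.8 = 432.5, so 433 per arm and 866 in all. Nothing below changes these numbers.

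**1. What the listed costs imply.** Follow-up health checks are offered to both arms (Compliance and loss to follow-up; Usual care). Training, brochures and counselling contacts arise only in the intervention arm. On this list the incremental cost is essentially positive, whatever happens to absence.

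**2. Scale of the uncounted item.** The documents give no prices, so all prices here are assumptions.
- Contact time (Outline of the intervention): (3×45 + 4×15)/60 = 3.25 h, up to (3×60 + 4×30)/60 = 5.0 h per man.
- At an assumed 75 euro per hour: 3.25×75 ≈ 244 to 5.0×75 = 375 euro. At an assumed 200 euro per absence day, break-even is 244/200 = 1.2 to 375/200 = 1.9 days. This leaves out training, brochures and travel, so it is a low estimate.
- At an assumed total intervention cost of 500 and 150 to 350 per day, break-even is 500/350 = 1.4 to 500/150 = 3.3 days. The net cost is 150 to 350 for 1 day less absence, -200 to +200 for 2 days, and -550 to +50 for 3 days. Without a value for absence it stays at 500.

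A difference of this order in the other direction would raise the cost by the same amounts.

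**3. The ratio interval: one example.** Inputs: 346 per arm (plan); effect in SD units, so SE = √(2/346) = 0.076; assumed cost difference 500 with SD 150 in the intervention arm, so SE = 150/√346 = 8.1.

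For an observed effect of 0.05 SD the ratio is 500/0.05 = 10,000. About 26% of resampled effects are negative, and the 2.5th and 97.5th percentiles of the ratio are about -82,000 and +86,000.

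The 95% range for the effect is 0.05 ± 1.96×0.076 = -0.099 to 0.199. Ignoring the small cost error, the ratios compatible with it are those above 500/0.199 ≈ 2,500 and those below 500/(-0.099) ≈ -5,050, joined through infinity. The percentile interval contains the gap between -5,050 and 2,500, which the data speak against. It leaves out the extreme ratios near zero effect, which the data allow.

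| Observed effect (SD) | Ratio | Percentile limits | Resampled effects below 0 |
|---|---|---|---|
| 0.05 | 10,000 | -82,000 to +86,000 | 26% |
| 0.10 | 5,000 | -39,000 to +49,000 | 9% |
| 0.15 | 3,333 | about 1,200 to 20,700 | 2.5% |
| 0.30 | 1,667 | 1,110 to 3,330 | under 0.1% |

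A second set of assumptions gives the same picture. With cost 300 (SE 60) and effect 0.20 (SE 0.15), effect/SE is 1.33, 9% of resampled effects are at or below zero, and the limits are about -11,500 and +14,300 (they move by a few hundred between runs).

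**4. How often this would happen.** From 2,000 simulated trials per row, with the inputs of step 3. Straddling means that more than 2.5% of resampled effects lie on each side of zero.

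| True effect (SD) | Trials straddling zero | Coverage of nominal 95% percentile interval |
|---|---|---|
| 0 | 95% | 0% (true ratio infinite) |
| 0.01 | 95% | 78% |
| 0.02 | 94% | 89% |
| 0.05 | 89% | 96% |
| 0.10 | 73% | 97% |
| 0.15 | 51% | 97% |
| 0.20 | 25% | 97% |
| 0.30 | 2% | 97% |

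Coverage fails only very close to zero. Interpretation fails over a wider band, up to roughly 0.15 to 0.2 SD. A Fieller set covers 94 to 96% throughout.

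**The case against.** - **The list may not be the total.** It describes what the principal investigator records. Absence and other care are reported by participants, so their absence from the list does not prove exclusion, and total costs leaves room for them. This stands. It is why the finding is an undefined term and a ratio limited on the only list given, not a demonstrated exclusion.
- **A reader might infer that the trial cannot show any benefit on absence.** The documents do not support that. Absence is an outcome in both arms and the analysis covers all outcome measures. Only its money value is missing from the ratio.
- **A reader might infer that the stated question is the employer's return.** It is not. The employer sentence is conditional on effectiveness, and the cost-effectiveness sentence concerns uptake by the occupational health services, for which an intervention-cost view is defensible. That view should therefore be kept.
- **A reader might infer that the bootstrap intervals are invalid in general.** The type is not given, percentile coverage is adequate away from zero, and a plane is planned. All true. The plane, if it shows the resampled pairs, displays the uncertainty, but a ratio interval beside it still cannot be read as a range when the pairs cross zero.
- **Prices and perspective may sit in a fuller document.** This is fair for unit prices. It does not remove the difference in wording between the two sections or the stated rule of putting intervals on ratios.

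**Conclusion.** The point holds in limited form. The two sections do not agree on, or do not define, the costs in the numerator. On the list given, the ratio cannot respond to absence or other care in either direction. Under the assumed prices, roughly 1 to 3 days of absence per man would offset the intervention cost, so the choice could decide the sign of the cost difference.

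The plan to put confidence intervals on the ratios is a poor rule for biomedical effects that may be modest. With 346 per arm and the assumed costs, resampled effects would straddle zero in 73% of trials at a true effect of 0.10 SD and in 51% at 0.15 SD, but in only 2% at 0.30 SD.

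All money values and effect sizes are assumptions, and the interval figures assume a percentile method. This concerns a secondary analysis.

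**What to change.** In Data analysis, drop confidence intervals for the ratios. Show the joint bootstrap cost and effect pairs on the planned plane for each outcome, with incremental net benefit (threshold × effect difference - cost difference) or acceptability curves over a stated range of threshold values per unit of effect. Net benefit has no denominator, so it stays interpretable when the effect is near zero.

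In Cost-effectiveness and Data analysis, use one definition of total costs and name the perspective. Report two results:
1. intervention costs only, as now listed;
2. those costs plus valued absence days in both arms, and other care where the co-intervention items record volumes that can be costed.

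The cost is wording, unit prices and a threshold range, none of which the documents give. Absence needs no new questionnaire. Whether the co-intervention items yield usable volumes has to be checked. Cost intervals in the second result will be wider, because absence is skewed.
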